### 8.4 Recording of any AE/SAEs

The study defines AEs and SAEs per the national guidelines which are also found in the Serious Adverse Events handbook created by RTI ENVISION and the Task Force for Global Health:

**“Adverse event from MDA (AE-F-MDA)** is a medical event that takes place in an MDA program, causes concern in the medical and wider community and is believed to be caused by the drug(s) used. It can be caused by either administration of the drug or by a coincidental event that by chance happened after drug administration. Most AEs-f-MDA (adverse events from MDA) are self-limiting and treatable using simple remedies and are not usually required to be reported to national or international regulatory authorities.

**Serious Adverse Event (SAE)** is a regulatory term describing any untoward medical occurrence with any of the following characteristics:

- Results in death;
- Requires in-patient hospitalization;
- Results in persistent or significant disability;
- Is life-threatening; or
- Results in a congenital anomaly/birth defect.”

All adverse events will be recorded and followed up by the nurses on the team. The reporting of adverse events will be systematic and comply with national AE/SAE reporting guidelines to avoid any bias related to the wording of the question(s).

While the difference between “adverse events” and “serious adverse events” have been described above, there is also a level of severity which the study will also monitor: “The term “severe” is often used to describe the intensity (severity) of a medical event, as in the grading “mild”, “moderate”, and “severe”; thus a severe action need not be serious.” Reported adverse events will be classified according to their intensity (none, mild, moderate, and severe).

- Mild: easily tolerated, does not interfere with daily activity,

- Moderate: uncomfortable enough to interfere with daily activity,
- Severe: precludes daily activity (Given that a “severe” adverse event includes inability to complete daily activities, it will be classified as a possible SAE for the purposes of this study.)

The evolution of older complaints will be classified as: exacerbated, ongoing, and improved or resolved/none.

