The causal relationship of serious adverse events observed with the triple therapy will be assessed as: *Unrelated, Unlikely, Likely*. The study will utilize information collected by the clinical nurses using the “Conduct an AE Investigation” steps detailed in the Serious Adverse Event Handbook. It is important to note that the study will not follow-up “minor” or “moderate” adverse events up with the full investigative checklist prescribed by the handbook but will reserve this for “severe” adverse events and SAEs. The PI, supervisors, and independent monitors will meet to review these determinations. If the supervisory group questions the results of the clinical nurses’s investigations, it will perform its own investigation of the report as an addendum to the original report. Incidences will be analysed based on preferred terms and body system levels. “Severe” adverse events and SAEs occurring during exposures will be analysed based on 3 levels of selection per pre-existence and causality:

- Treatment emergent signs and symptoms (TESS), i.e., all AE during exposure to treatment or that were not pre-existing
- TESS without causality ‘unlikely’
- TESS with causality ‘likely’

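### Section 8.5 defines treatment-emergent severe events with an 'or' that leaves the pre-existence condition unable to exclude anything

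*Protocol*

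**What the plan says.** The last part of protocol section 8.5 sets out how severe AEs and SAEs will be analysed. The lead-in says that severe "adverse events and SAEs occurring during exposures will be analysed based on 3 levels of selection per pre-existence and causality". Three tiers follow:

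- Tier 1: "Treatment emergent signs and symptoms (TESS), i.e., all AE during exposure to treatment or that were not pre-existing".
- Tier 2: "TESS without causality ‘unlikely", that is, tier 1 less the events with that rating.
- Tier 3: "TESS with causality ‘likely", that is, only the tier 1 events with that rating.

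The same section gives the causality scale as Unrelated, Unlikely and Likely.

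Pre-existing complaints are recorded elsewhere. Form 1 (Appendix 2, item 2.1) lists 28 named symptoms to be checked before treatment, and item 2.2.2 rates the main complaint. Section 8.4 adds a scale for what becomes of them: "The evolution of older complaints will be classified as: exacerbated, ongoing, and improved or resolved/none". The surveillance form (Appendix 4) applies that scale at item 3.2.7.1 and has a separate table for existing symptoms that got worse (items 3.2.7.5 and 3.2.7.6). The tier 1 definition refers to none of these.

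**The concern.** The lead-in promises a filter on pre-existence. The definition offers two ways to qualify, joined by 'or', and the lead-in has already imposed the first of them. A filter that every candidate has passed before it is applied selects nothing.

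At stake is which severe events are reported as treatment-emergent in a trial whose primary outcome is safety. Illness that was there before dosing may be counted with events that began after it. Two analysts could also produce different tier counts from the same data: one following the literal text, the other the evident intention.

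**Working it through.** The protocol states no figure on this point, so the check is logical.

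**Step 1. Inputs.** Each event is described by whether it occurred during exposure, whether it was pre-existing, and its causality rating (Unrelated, Unlikely, Likely). That gives 2 × 2 × 3 = 12 combinations. The lead-in admits only the six that occurred during exposure.

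**Step 2. Apply the tiers to those six.** The literal rule is (during exposure) or (not pre-existing). The comparison rule is (during exposure) and (not pre-existing).

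| Event during exposure | Rating | Tiers under 'or' | Tiers under 'and' |
|---|---|---|---|
| Pre-existing | Unrelated | 1, 2 | none |
| Pre-existing | Unlikely | 1 | none |
| Pre-existing | Likely | 1, 2, 3 | none |
| New | Unrelated | 1, 2 | 1, 2 |
| New | Unlikely | 1 | 1 |
| New | Likely | 1, 2, 3 | 1, 2, 3 |

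Under 'or', the pre-existing rows match the new rows exactly, so pre-existence makes no difference to any tier. Under 'and', all pre-existing events drop out. That goes too far the other way, because a complaint that worsened after dosing would be lost as well.

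**Step 3. A side result.** Tier 2 removes Unlikely but keeps Unrelated, for new and pre-existing events alike. The rating furthest from a drug effect survives a step that removes a nearer one.

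**Step 4. Can a pre-existing complaint reach this analysis?** Two routes are open.

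- Section 8.4 defines an SAE by its outcome and requires no belief that a drug caused it.
- In Appendix 4, a participant who answers Bad has the pre-treatment complaints reviewed and graded 0 to 3, with 3 meaning major or severe. The grade is current severity, not change. The note below the table sends reported severe effects on to the 4.3 questions, which are the SAE form (Appendix 5). A complaint rated major before dosing can therefore be coded severe afterwards.

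**Step 5. Direction of the effect.** The following is an illustration only; none of these rates is in the protocol. Let g be the proportion with a pre-existing severe complaint that is counted, equal in both arms, and let r be the true emergent severe rate, independent of g. The counted rate is 1 − (1 − g)(1 − r). Take r = 0.1% in one arm and 0.2% in the other, a true ratio of 2.0 and a true difference of 0.1 percentage points.

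| g (assumed) | Counted rates | Ratio | Difference (points) |
|---|---|---|---|
| 0.2% | 0.300% vs 0.400% | 1.33 | 0.100 |
| 0.5% | 0.600% vs 0.699% | 1.17 | 0.100 |
| 1.0% | 1.099% vs 1.198% | 1.09 | 0.099 |

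With equal background the ratio shrinks, while the absolute difference barely moves.

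**The case against.** The strongest reply is that an unchanged old complaint is not an AE in this protocol. Section 8.4 describes an AE as something that "causes concern in the medical and wider community and is believed to be caused by the drug(s) used", and it puts older complaints on their own scale. Appendix 4 offers the answer Same as before, and its table for existing symptoms is headed as covering worsened ones. A participant who reports no change has no clear route into an AE table. This stands for many ordinary complaints and limits how often the fault will matter. It does not remove it, because the SAE definition requires no causal belief and the table for Bad responders grades current severity.

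A reader might also infer more than the text supports:

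- *That pre-existing complaints are counted in every tier.* They are not. Only those rated Likely reach tier 3, and those rated Unlikely are in tier 1 alone.
- *That new events outside exposure are counted.* Tier 1 taken alone would admit them, but the lead-in has already excluded them.
- *That severe counts are inflated by a known multiple, or that a true difference is hidden.* The protocol gives no background rate. With equal background the absolute difference is nearly unchanged, and the trial's margins are absolute differences. Dilution of the ratio is the most that can be said.
- *That the pre-treatment symptom check serves no purpose.* It still feeds the evolution grading and the worsened-symptom table. It is idle only in this analysis.

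The scope is narrow. The tiers do not enter the primary comparison, and the DSMB triggers in section 8.5 do not use them.

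**Conclusion.** The point holds. The tier 1 definition contradicts the selection that its lead-in announces, and on a literal reading pre-existence excludes no event. Pre-existing severe complaints recorded as AEs or SAEs stay in tier 1 at all three ratings, in tier 2 at two of three, and in tier 3 at one of three.

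The consequence is background illness in the severe AE and SAE counts and a diluted relative difference between arms. Its size cannot be derived from the protocol, and the figures in the illustration are not estimates. That illustration assumes equal background in both arms. The protocol does not secure this, because under section 8.8 the control arm goes through distribution and active surveillance twice, which may give persisting complaints a second chance of being recorded.

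The primary comparison of the proportion with any AE, the 1.5% margin and the sample size are unaffected.

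**What to change.** Replace the tier 1 line in section 8.5 with:

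> TESS: severe AEs and SAEs during exposure that either (a) were not present at the pre-treatment interview (Form 1, 2.1) and began after the first study dose, or (b) were present at that interview and worsened after dosing, i.e. graded exacerbated (3.2.7.1) or recorded as worsened in the existing-symptoms table (3.2.7.5 to 3.2.7.6). Unchanged pre-existing complaints are not TESS.

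Branch (b) must not require onset after dosing, since a complaint already present could never meet that. It needs both form items: 3.2.7.1 is prompted only for participants who answer Fine, so a rule tied to that grade alone would miss those who answer Bad.

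In the same edit, make tier 2 exclude Unrelated as well as Unlikely.

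The cost is a few lines of protocol text, with no new data item. One instruction on the form is advisable: enter a symptom in the existing-symptoms table only if it worsened, because the grade there records current severity and Form 1 rates only the main complaint before treatment.

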## 8.6 Co-administration Team Composition

Both the trial and the control arm will be allocated 4 distribution teams. Each distribution team will be comprised of 8 people. This will result in 32 people on each arm with both arms together equalling 64 people. In addition, the study will assign an independent monitor to each arm of the study who will travel among the four teams and ensure that the study is implemented per protocol and with no bias.

### 8.6.1 Team breakdown:

2 clinical nurses

2 HEWs (or 1 HEW and 1 health officer)

3 HDA

1 supervisor

**TOTAL: 8 members of on each team x 8 teams= 64 total team members**

### 8.6.2 Team Description

**2 clinical nurses:** Before the drugs are given, the nurses (one for each line) will confirm that the beneficiaries have given assent and that there is a corresponding signature/mark for the community leader. The nurses will fill out the register questionnaire detailed in the appendix that establishes whether or not any previous medical conditions exist. Once the MDA portion is complete, the nurses will remain at the distribution site for the night in case any of the beneficiaries need to self-report adverse effects. The next morning, the nurses, with the aid of the HDA, will conduct house-to-house follow up visits according to the schedule detailed in the *Co-administration Schedule* section.

**2 Health Extension Workers:** HEWs (one for each line) will be responsible for actually co-administering the drugs to consenting/assenting beneficiaries. The HEW will assign the dosage according to different dose poles for IVM and azithromycin as well as the single dose of Albendazole. The HEW will be responsible for organizing the MDA schedule within the cohort as explained in Figure 1. The HEW will also be responsible for providing access for any reported AE/SAEs through passive follow-up should any community members have any complaints throughout the one month period.

**3 HDA:** Three members of the Health Development Army (one for each line and one to give line assignments to beneficiaries) will have the responsibility of assisting the HEW with community mobilization and crowd control once the co-administered MDA actually begins. These HDA members will also acts as guides to help the clinical nurses go house to house during the follow up day. The HDA will stay within each gote as this is their station. They will be within the community they are assigned for the rest of the study to provide passive surveillance.

**1 supervisor:** The study will assign one supervisor from the RHB, zonal office, or woreda health office to each team to ensure that the protocol is followed. The supervisors will report to the study managers who will travel between all the teams and provide general oversight and technical guidance.

### 8.6.3 External monitoring

The study will also invite independent study monitors to ensure that the trials is conducted in an un-biased manner. This will help encourage adoption of the triple drug therapy by the WHO assuming non-inferiority is established. The study team will invite these independent monitors from both academic institutions within Ethiopia and abroad. At a minimum, the study will assign one independent monitor to each arm of the trial.

### 8.6.4 Audits and Inspections

The study may be subject audit by the London School of Hygiene & Tropical Medicine under their remit as sponsor, the Study Coordination Centre and other regulatory bodies to ensure adherence to GCP.

## 8.7 Co-administration Team Composition

The co-administration study will place additional safety measures in addition to the National SAE/AE reporting protocol. As mentioned in the training section, all health extension workers and Health development armies within the targeted kebeles will be provided with a specially adapted training before the MDA addressing how to conduct the directly observed co-administration and how to administer the study questionnaire. Two clinical nurses for each of the four teams working in a cohort will supervise the co-administration and conduct the next-day follow up for all the beneficiaries that received triple drug administration. The study will also place a study physician at the study site for the duration of the 14-day co-administration exercise. The nurses will conduct active house to house surveillance starting the morning after the study and will regularly communicate with the assigned study physician stationed within the kebeles. A nearby referral centre (district/regional hospital) will be informed and on stand-by should any reactions occur. The study team will have three dedicated four-wheel drive cars to allow supervisors and study physician to travel between the targeted gores and evaluate the work of the teams and for use in case evacuation to the health facility might become necessary.

## 8.8 Co-Administration Schedule

*The study will have two cohorts control arm, which will receive the usual MDA, and study arm which will receive the triple co-administration. Each arm will have approximately 6,800 people, 42 Gotes. Primarily, the clustering will be made by geography where 42 adjacent Gotes will be in one and the other 42, in another. Which cluster will be the control or study arm will be decided by simple lottery method.*

*After decision on the study arms, the study team will conduct the training and the actual co-administration for a 17-day period (three days for training and 14 days for actual co-administration and surveillance). In total, the entire study will take 45 days to complete.*

**On Day 1**, after the three-day co-administration training module described above, 60 households (HH) or roughly 300 people will be targeted for MDA subjects included in the study will receive concomitantly azithromycin (up to 1 g or four 250 mg tablets), ivermectin (up to 12 mg or four 3 mg tablets) and albendazole (one 400 mg tablet per included subject irrespective of height and age). This will mean that the four teams in the trial arm and the four teams in the control arm will have treated 1200 people each (300 x 4) by the end of Day 1. Teams will remain at the location of the MDA for the entire day and night on standby in case there are any immediate complaints from the targeted beneficiaries. Note that, as described in the “Intensified medical access precautions” section, a medical doctor will remain centrally located between within the woreda throughout the 14 actual days of distribution in the unlikely occurrence of a reaction to the medication.

**On Day 2**, the clinical nurses on each team, led by the three HDA members, will travel to all 60 households within their team’s catchment area to confirm that all 300 persons that received drugs on Day 1 are all healthy and to document any AEs/SAEs that may have occurred. This will also serve as opportunity for a person-to-person coverage survey for later analysis. At the end of the day, the four teams from each arm, together with the independent monitors, PI, supervisors, etc. will meet and discuss if there were any results that should cause concern. While the clinical nurses conduct the house-to-house visits, the HEWs on each team will move to the next group of 60 households targeted for the Day 3 MDA and mobilize that community.

**On Day 3**, each team will treat an additional 300 people (60HH) following the same regimen as was described on Day 1. By the end of Day 3, the four teams in the trial arm and the four teams in the control arm will have treated 1200 people each (300 x 4) Together with the people treated on Day 1, this will equal 2400 people out of the 16, 000 people targeted for treatment.

**On Day 4**, the clinical nurses on each team will once again travel to the 60 households of the 300 beneficiaries within their catchment area and follow the procedure described on Day 2. All 1,200 people treated on Day 3 will receive a house visit. The HEW will mobilize the community targeted for MDA on Day 5.

**On Day 5**, each team will treat an additional 60 households or roughly 300 people. Across the four teams in each arm, this will equal roughly 1,200 people each (4 teams x 300 people) and, when added together with the populations treated on Day 1 and Day 3, will equal 3,600 people (Day 1: 1,200 + Day 3: 1,200 + Day 5: 1,200= 3600 people).

**On Day 6**, the clinical nurses in all six teams will once again follow up with all people treated on Day 5. *Note on Day 6 and 7, the doctor as well as the PI and a woreda health officer will travel back to the communities treated on Days 1-5 to gather any passive AE reports from the HDA members originally involved in the distribution to that community.*

**On Day 7, Day 9, Day 11, Day 13:** same MDA distribution as described on Day 1. When combined with the 5,400 people from Days 1,3, and 5, this will result in a total of 12,600 people targeted for treatment. (5,400+ 100 +1800 +1800+1800= 12,600).

**On Day 8, Day 10, Day 12, and Day 14** Same active house to house follow-up method described on Day 2, 4, and 6.

By the end of Day 14, the actual triple-drug co-administration will be completed. On Day 14 and 15, the medical doctor, PI and woreda health officer will once again travel to the communities treated between Day 7 and 14 to gather any reports from the passive

surveillance carried out by the HDA. The HEWs and clinical nurses will continue observation in Kofele for an additional 15 days per the following schedule:

**On Days 15 and 16**, the HEW and clinical nurses will remain stationed at a central location between the targeted gores in case any of the beneficiaries has symptoms to report that might be linked to the co-administration. This will be a system of passive, self-reporting follow-up.

**On Day 17, 18**, the clinical nurses and HEW from each of the original four teams will perform one last house to house follow up of all the households that received the triple drug administration. (400 HH x 4 teams = 1600 HH) This will be the last active follow-up step.

**Day 19-30**, the HEWs will maintain the reporting form for another two weeks in the event of any additional complaints from the targeted beneficiaries. This will be completely passive and the HEW will only log complaints if they are reported by a beneficiary. On Day 30, all of the co-administration registers and forms will be collected for data analysis from the HEWs.

Note that in the “standard MDA” control arm, the process described above will be conducted twice. First, IVM/ALB MDA will take place for with 14 days of active surveillance then the Trachoma MDA will take place for 14 days of active surveillance. Passive surveillance will continue in the control arm for two weeks after that.

Once the 45th day of the study is reached in Oromia, the field implementation portion of the study will be complete. The DSMB will review the final data before making a recommendation on how the remainder of the population in the woreda should be treated. Should the DSMB and the FMOH agree, the remaining 4-5000 beneficiaries within Homesha will be targeted for co-administration. However, at this juncture, the RCT will be over. The study will move to strictly observational with the same enhanced supervision in place.

Table 3: Follow up Schedule for both the Trial and the Control Arms of the Study

|                                                    | Day 1 | Day 2 | Day 3 | Day 4 | Day 5 | Day 6 | Day 7 | Day 8 | Day 9 | Day 10 | Day 11 | Day 12 | Day 13 | Day 14 | Day 15 | Day 16 | Day 17 | Day 18 | Day 19-30 | Day 31 |
|----------------------------------------------------|-------|-------|-------|-------|-------|-------|-------|-------|-------|--------|--------|--------|--------|--------|--------|--------|--------|--------|-----------|--------|
| Actual Distribution                                |       |       |       |       |       |       |       |       |       |        |        |        |        |        |        |        |        |        |           |        |
| Next Day Follow-up                                 |       |       |       |       |       |       |       |       |       |        |        |        |        |        |        |        |        |        |           |        |
| One week follow up                                 |       |       |       |       |       |       |       |       |       |        |        |        |        |        |        |        |        |        |           |        |
| 14 Day Follow up                                   |       |       |       |       |       |       |       |       |       |        |        |        |        |        |        |        |        |        |           |        |
| Passive Surveillance                               |       |       |       |       |       |       |       |       |       |        |        |        |        |        |        |        |        |        |           |        |
| DSMB Review (or as needed via charter description) |       |       |       |       |       |       |       |       |       |        |        |        |        |        |        |        |        |        |           |        |

Figure 1: Randomization and MDA distribution Plan in Trial and Control arms

[figure not shown]

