| Title              | Safety of the co-administration of azithromycin, albendazole and ivermectin versus standard treatment regimens during mass drug administration (MDA) in Ethiopia: a cluster-randomized trial                                                                                                                                                                                                                                                                                                                                                                                                                                                                                                                                                                                                                 |
| Objective          | To establish the safety profile, assess the community acceptance, and weigh the economic advantages of a three-agent MDA combining azithromycin, albendazole (Alb), and ivermectin (Ivm) in comparison to the standard MDA regimen which separates the administration of azithromycin from the dually administered ivermectin and albendazole by a period of two weeks.                                                                                                                                                                                                                                                                                                                                                                                                                                      |
| Design             | A cluster-randomized non-inferiority trial to assess the safety, local acceptance, and economic advantages of combined MDA with azithromycin, albendazole, and ivermectin in one district in Oromia, Ethiopia. Within this district, a study group of 8,000 people will receive the triple drug co-administration. A control group of 8,000 people within the same district will receive the standard MDA treatment beginning with Ivm/Alb followed two weeks later with azithromycin. The study will randomly sort sub-district communities ( Gotes ) into the trial arm and the control arm. The study will compare the “baseline” of adverse events (AEs) and severe adverse events (SAEs) between the two arms to determine if the triple drug therapy is not inferior to the standard treatment. |

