The study will require a power of 90% and a two-sided 95% confidence interval for the difference between rates. Given that gotes will be randomly selected from within the same woreda, have all had the same number of years of treatment with each drug, and share the same cultural and environmental factors, we will assume a low variability between each cluster. In case there are unforeseen differences between the clusters, we will include a variance between 6-8%. Conservatively assuming that each gote has a population of 190 individuals, the study will require at least 36 gotes in each study arm to reach 13,600. To take non-compliance, etc. into account, the study will randomize the 42 gotes into each study arm to reach 8,000 participants in each arm from the list of gotes in Kofele woreda into the control and study arms until each arm has 8,000 participants (to account for non-compliance, etc.). Gotes will be chosen via the RANDNUM function in excel. The randomization itself will be conducted via public randomization ceremonies.

Table 2: Assumption Summary

|                                                               |                                                           |
|---------------------------------------------------------------|-----------------------------------------------------------|
| Adverse event prevalence                                      | 7% on average                                             |
| Acceptable adverse event percentage during co-administration: | 8.5%                                                      |
| Delta                                                         | 1.5%                                                      |
| Variance                                                      | Adverse event prevalence between clusters will be 6-8%    |
| Power                                                         | 90%                                                       |
| CI                                                            | 95%                                                       |
| Minimal Number of Gotes Required for each arm                 | 36                                                        |
| Population per cluster                                        | 190 individuals per cluster (gote) on average             |
| Total Population of Study                                     | 13,600 (Rounded to 16,000 for refusals/loss to follow up) |

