### 8.9 Data Collection and Statistical Analysis

Data about individual participant will be collected by the study team using structured questionnaires and coded, de-identified labels which will be held in strict confidence. All results will be presented in a way that does not allow individuals to be identified. No information concerning the study or the data will be released to any unauthorized third party. These questionnaires are presented in the appendix of this protocol. The study team will rely on electronic data capture and will convert these forms to the ODK electronic format at the London School of Hygiene and Tropical Medicine.

Table 4: Data Collection Summary for AE reporting

| Forms                                                                                  | Timeline                                                                                                           | Person responsible for filling out the form |
|----------------------------------------------------------------------------------------|--------------------------------------------------------------------------------------------------------------------|---------------------------------------------|
| Informed Consent                                                                       | Pre-MDA Census days and Distribution Day                                                                           | HEW/Clinical Nurses                         |
| Socio-demographic/health Information                                                   | Distribution Day                                                                                                   | Clinical Nurses                             |
| Study drug registry                                                                    | Distribution Day                                                                                                   | Clinical Nurses                             |
| Contra-indication/AEs reporting to the Co-Administration team (HEW and clinical nurse) | Day 2, Day 4, Day 6, Day 8, Day 10, Day 12, Day 14, Day 17+18 follow up or at any time during passive surveillance | Clinical Nurses/HEW                         |
| Contra-indication/AEs reporting to the local health post (HEW)                         | Day 19-30                                                                                                          | HEW                                         |

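### Section 8.8 assigns two blocks of 42 adjacent gotes by one lottery, contradicting the gote-level randomisation in the summary and 8.1 on which the sample size and confidence interval depend

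*Protocol*

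**What the plan says.** The protocol describes the allocation in three places.

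- **Protocol summary, Design row.** The unit is the sub-district community: "The study will randomly sort sub-district communities" into the two arms.
- **Section 8.1.** "the study will randomize the 42 gotes into each study arm to reach 8,000 participants in each arm", with gotes taken from the woreda list by a spreadsheet random-number function and a public draw. Table 2 in the same section uses the word cluster for a gote of 190 people.
- **Section 8.8, opening paragraph.** "Primarily, the clustering will be made by geography where 42 adjacent Gotes will be in one and the other 42, in another". The random step follows: "Which cluster will be the control or study arm will be decided by simple lottery method". Here the word cluster can only mean a 42-gote block.

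The analysis is in section 8.9: a clustered logistic regression, with the upper limit of the 95% interval for the difference in adverse event rates compared with a margin of 1.5 percentage points.

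**The concern.** These are two different designs. Under 8.1 there are 84 randomised units, and chance differences between gotes average out and are measured by the spread among gotes within each arm. Under 8.8 there are two units, one per arm. Whatever distinguishes one half of the study area from the other (age mix, background illness, readiness to report symptoms) then sits entirely in the treatment contrast. Adjusting for clustering by gote does not remove it, because the gotes within a block share it.

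The margin is narrow, so a modest area difference could produce a false claim of non-inferiority or hide a true one. The final data also inform whether the rest of the woreda receives the triple regimen. The fault cannot be repaired after the draw, and as written the field team could follow either section.

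**Working it through.** **Inputs.** From 8.1 and Table 2: adverse event rate 7%, margin 1.5 points, power 90%, two-sided 95% interval (one-sided 2.5%), 190 people per gote, and adverse event rates of 6-8% across gotes. I read that band as the mean plus or minus 2 SD, so the between-gote SD is 0.5 points. A block-level SD is not given anywhere.

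**Step 1. Reproduce the plan's figure, with the gote as the unit.** The standard unmatched cluster-trial formula is

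c = 1 + (1.960 + 1.282)² × 2 × [p(1 − p)/m + SD²] / margin²

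- p(1 − p)/m = 0.07 × 0.93 / 190 = 0.000343
- SD² = 0.005² = 0.000025
- c = 1 + 10.51 × 2 × 0.000368 / 0.000225 = 1 + 34.3 = 35.3, rounded up to **36**
- 36 × 190 = 6,840 per arm and 13,680 in total, as in section 6

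The plan's number is therefore that of a design with the gote as the independent randomised unit.

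**Step 2. Precision under gote-level randomisation.** SE = √(2 × 0.000368 / c).

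- 36 gotes per arm: SE 0.452 points, power Φ(1.5/0.452 − 1.96) = 91%
- 42 gotes per arm: SE 0.418 points, power Φ(1.5/0.418 − 1.96) = 95%

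**Step 3. Units under 8.8.** Two blocks less two arms leaves 0 degrees of freedom for between-block variance. It cannot be estimated from the trial.

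**Step 4. What the gote-based interval then omits.** Let τ be the SD of an effect shared by all gotes in a block. The true SE is √(SE² + 2τ²), while the reported SE stays at 0.418 points.

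- One-sided error at a true excess of 1.5 points: Φ(−1.96 × SE / true SE)
- Power at true equality: Φ((1.5 − 1.96 × SE) / true SE)
- Example, τ = 0.5: true SE = √(0.175 + 0.5) = 0.822, and the error is Φ(−1.96 × 0.418/0.822) = Φ(−1.00) = 15.9%

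With 42 gotes per arm, and τ assumed:

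| τ (points) | True SE (points) | One-sided error | 95% coverage | Power at equality |
|---|---|---|---|---|
| 0 | 0.42 | 2.5% | 95% | 95% |
| 0.25 | 0.55 | 6.7% | 87% | 89% |
| 0.5 | 0.82 | 15.9% | 68% | 80% |
| 1.0 | 1.47 | 28.9% | 42% | 68% |

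With 36 gotes per arm, the errors for τ = 0.25, 0.5 and 1.0 are 6%, 15% and 28%.

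**A side check.** Section 8.8 also says "Each arm will have approximately 6,800 people, 42 Gotes". That is 8,000 less 15%, so I read it as the number left after losses and not as a further contradiction.

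**The case against.** The strongest reply is that 8.8 is the outlier. The summary and 8.1 agree on the gote, the sample size was computed for the gote, and the block wording sits in the preamble to a scheduling section, where adjacency may have been meant only to ease logistics. Figure 1, which shows the randomisation plan, is not available to settle it. This stands to the extent that block allocation cannot be called the settled design, and the interval is not invalid without condition. It does not remove the defect, because 8.8 as written assigns treatment by block.

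A second reply is that 8.1 gives reasons to expect little variation: one woreda, the same treatment history, shared culture and environment. Those are grounds for thinking τ is small. However, 8.1 applies them to gotes, no section applies them to two halves of the area, and under 8.8 the data could not test them.

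Three stronger readings are tempting and are not supported:

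- **A 1-point gap between blocks follows from the 6-8% band.** The band describes gotes. If gotes varied independently with SD 0.5 points, the two 42-gote means would differ with SD 0.5 × √(2/42) = 0.11 points, and a 1-point gap would be about nine SDs. Such a gap needs a shared area effect, which the documents do not quantify.
- **No result could be significant, because two allocations permit a one-sided randomisation p-value no lower than 0.5.** The arithmetic is right, but the protocol plans a regression and not a randomisation test.
- **Separate teams per arm, or consent given after the draw, are part of this fault.** Both would arise equally under gote-level randomisation. They are separate questions.

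**Conclusion.** The concern holds as an internal contradiction about the randomised unit, with a serious consequence if the wrong section is followed. Sections 8.1 and 8.8 cannot both be carried out, and the sample size and the primary interval fit only 8.1. Under 8.8 the interval would be correct only if between-block variance were zero. That conclusion needs no assumed value.

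Its numerical size does. For block SDs of 0.25 to 1.0 points, the one-sided error would be about 7% to 29% in place of 2.5%, and coverage about 87% to 42% in place of 95%. These are scenarios with 42 gotes of 190 per arm and a between-gote SD of 0.5 points. They are not estimates from the documents. The passages must be reconciled before the draw.

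**What to change.** Delete the two sentences in 8.8 on adjacent blocks and the lottery. Replace them with a statement that the 84 gotes are randomised individually, 42 to each arm, by the method in 8.1. Stratifying by kebele is optional. Keep the gote as the cluster in the 8.9 analysis, use the word cluster for the gote throughout, and check that Figure 1 shows the same scheme.

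The sample size does not change: power is 91% with 36 gotes of 190 per arm and 95% with 42. The cost is practical. Gotes of the two arms will be interspersed, so teams will travel more and their routes and daily schedule must be reworked. Neighbouring gotes will be on different regimens, but doses are directly observed, which limits crossover between arms.
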